**Aim 1: psychosocial stressors**						
	Chronic stress: Adult Stress and Adversity Inventory [100]		✓	✓	✓	✓
	Perceived discrimination: Detroit Area Study Discrimination Scale [101]		✓	✓	✓	✓
	Perceived racism: Index of Race-Related Stress–Brief Version B [102]		✓	✓	✓	✓
	Subjective social status: MacArthur Scale of Subjective Social Status [103]		✓	✓	✓	✓
**Aim 1: response to chronic stress exposure**						
	Current perceived stress: Perceived Stress Scale [104] and Stress Overload Scale [105]		✓	✓	✓	✓
	Depressive symptoms: Beck Depression Inventory ([name], unpublished data, November 2017); depressive symptoms: Patient Health Questionnaire-9 [106]		✓	✓	✓	✓
	Anxiety: General Anxiety Disorder-7 [107]					
	Fatigue: PROMIS^e^ Fatigue Short Form 8a [108]		✓	✓	✓	✓
	Sleep disturbance: PROMIS Short Form v1.0 [109]		✓	✓	✓	✓
	Inflammatory burden: salivary CRP^f^, TNF-α^g^, IL-6^h^, IL-1β^i^, IFN-γ^j^, and CRP^k^ (Human High Sensitivity Cytokine B Premixed Magnetic Luminex Performance Assay [R&D Systems])		✓	✓	✓	✓
**Aim 2: Coping strategies**						
	Coping: Ways of Coping Questionnaire [110]		✓	✓	✓	✓
	Coping with discrimination: Coping with Discrimination Scale [111]		✓	✓	✓	✓
	Internalizing racism: Appropriated Racial Oppression Scale [112]		✓	✓	✓	✓
	Resistance and empowerment: Resistance and Empowerment Against Racism Scale [113]		✓	✓	✓	✓
**Covariates and descriptive measures**						
	Early life adversity: Childhood Trauma Questionnaire [114]		✓			
	Ethnic identity: Vancouver Index of Acculturation [115]		✓			
	Health behaviors, anthropometrics, and brief medical history: Block Brief 2000 Food Frequency Questionnaire [116]; National Institute of Nursing Research Social Determinants of Health Survey [117]; Self-Administered Comorbidity Questionnaire [118]; blood pressure, height and weight, body fat percentage, and body water percentage [119]; Alcohol, Smoking, and Substance Involvement Screening Test [120]; Life Events Checklist-7 [121]; and Race-Related Events Scale [122], health behaviors, anthropometrics, brief medical history, and demographics		✓	✓	✓	✓
	Intervention and active control group cohesion: 5-Item Engaged Scale from Group Climate Questionnaire [96]			✓	✓	✓

^a^T0: baseline.

^b^T1: midintervention.

^c^T2: intervention completion.

^d^T3: 6 months after intervention completion.

^e^PROMIS: Patient-Reported Outcomes Measurement Information System.

^f^CRP: C-reactive protein.

^g^TNF-α: tumor necrosis factor–alpha.

^h^IL-6: interleukin-6.

^i^IL-1β: interleukin-1beta.

^j^IFN-γ: interferon-gamma.

^k^CRP is not measured using the Luminex Performance High Sensitivity. Cytokine Magnetic Panel B MultiPlex but rather an Enzyme-Linked Immunosorbent Assay kit from R&D Systems.

#### Inflammatory Biomarker Procedures

Saliva samples will be collected to measure inflammatory biomarkers because this method is less invasive than blood draws. Salivary CRP and proinflammatory cytokines (eg, IL-6, TNF-α, IL-1β, and IFN-γ) are associated with stress-related symptoms [46,82]. We will follow recent best practice recommendations for collecting salivary cytokines [123], including the use of the passive drool method for sample collection and returning specimens overnight on dry ice between sites. Saliva samples will be kept frozen at −80 °C before batch analysis.

#### Exposure Variables

Measurements of chronic stress (Adult Stress and Adversity Inventory), perceived discrimination (Detroit Area Study Discrimination Scale), perceived racism (Index of Race-Related Stress–Brief Version B), and subjective social status (MacArthur Scale of Subjective Social Status; Table 3) will be collected and analyzed as exposure variables. Trained interviewers will collect these data using an audio computer-assisted self-interview system [72].

#### Covariates

Several variables may influence or moderate the relationship between the intervention group and chronic stressors, stress-related symptoms, and inflammatory burden and coping mechanisms. For this reason, data on age, education, income, employment, height and weight, blood pressure, health behaviors, and early life adversities, as well as a brief medical history, will be collected at baseline and considered as covariates.

### Analytic Plan

#### Data Quality

Before data analysis, we will ensure the accuracy and integrity of the data by regularly reviewing and cleaning the data from both sites using frequency distribution to identify data entry errors. In addition, 50% of the data will be manually checked for accuracy. If the coding or entry error rate is higher than 2% for any individual test or instrument, all data for that particular test or instrument will be manually checked. Monitoring logs will be maintained for the following: (1) patients screened for participation (basic demographic information and reason for nonparticipation [for nonparticipants only]), (2) patient entry into the study, (3) timeliness of data collection, and (4) missing data. Regarding missing items from the psychometric measurements, each tool will be assessed for missing data, and, if appropriate, participants will be contacted to complete the missing items.

#### Statistical Analysis

Baseline demographics and clinical characteristics will be reported according to the CONSORT (Consolidated Standards of Reporting Trials) guidelines. The size of any chance group imbalances will be described, but no formal significance testing of group differences will be performed [124]. Generalized linear mixed models (GLMMs) will be used for analyses of outcomes due to their flexibility regarding the distribution of dependent variables (DVs) and their superiority over alternative approaches such as repeated measures ANOVA for longitudinal modeling with missing data. Data will be collected from participants at 4 time points (T0: baseline, T1: midintervention; 4 wk, T2: intervention completion; 8 wk, and T3: 6 mo after intervention completion). Time will be modeled as a fixed effect, and random intercepts and random slopes will be considered to account for within-individual differences and trends. The primary DVs include stress-related symptoms (current perceived stress, depressive symptoms, fatigue, and sleep disturbance) and biomarkers (ie, IL-6, TNF-α, IL-1β, IFN-γ, and CRP) to be modeled using GLMM. Before modeling, DVs will be plotted to choose an optimal distribution and link function for GLMMs and to identify potential floor or ceiling effects. For each DV, a GLMM will regress the follow-up DV on a group×time interaction, the baseline value of the DV, and covariates. Treatment assignment (group) will be a fixed effect, and adjusted means with SEs will be used to describe group differences. Random effects will be evaluated for site and cohort. Exploratory end points include coping (Ways of Coping Questionnaire and Coping with Discrimination Scale), internalizing racism (Appropriated Racial Oppression Scale), and resistance to racism (Resistance and Empowerment Against Racism), which will be DVs in separate GLMMs, as described earlier.

Covariate adjustment will be performed to account for explained variation in outcome variables [125]. Not all covariates considered may be necessary to include in the models to explain the bulk of the variation in DVs; therefore, a parsimonious subset will be chosen concerning multicollinearity, the strength of associations, and appropriateness for total sample size. Residual plots will be examined to determine whether transformations or other regression remedial measures are required to satisfy model assumptions. Although sample size calculations have accounted for potential attrition, analyses of end points will be conducted under the intent-to-treat principle. While every attempt will be made to capture all available data on participants, we may consider sensitivity analyses using model-based approaches (eg, multiple imputation) for missing data [126]. A detailed statistical analysis plan will be prepared and finalized by the study biostatistician before the database lock to promote the reproducibility and transparency of the analytic approach. Analyses will be performed using SAS (version 9.4; SAS Institute) and R (version 4.0.2 or later; R Foundation for Statistical Computing). Results reporting will include all preplanned analyses, and any post hoc analyses will be clearly labeled as such when we disseminate this work.

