**Methods:**

In this randomized controlled trial, we will randomize participants 1:1 to the 8-week, group-based RiSE program (intervention) or a health education program (active control group). Both programs will consist of synchronous classes on Zoom and will be led by experts. The primary end point will be stress at 6 months after the intervention, and the efficacy of RiSE will be evaluated for improving stress-related symptoms (current perceived stress, depressive symptoms, fatigue, and sleep disturbance), improving coping strategies, and reducing inflammatory burden in African American women at risk for CMD. Validated survey measures and inflammatory biomarkers will be assessed at baseline, midintervention, intervention completion, and 6 months after the intervention, and differences over time by intervention will be evaluated using mixed effects models.

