### Sample Size

We will enroll 300 participants and anticipate that at least 250 (n=125, 50% per arm) will have the 6-month postintervention follow-up data. For the primary end point of the Perceived Stress Scale (PSS), this sample size has >80% power to detect a 3-point difference in mean PSS scores at follow-up using an *F* test in an analysis of covariance. This assumes the R-squared value of 5 covariates, including baseline PSS, to be 0.3 and uses a significance level of α=.05. This calculation conservatively estimates the SD of PSS to be 10 points. Initial psychometric studies and norm groups analysis of the PSS reported SDs of 7.2 points in African Americans; relevant to the RiSE study, group SDs ranged from 6 to 10 points from a pilot trial involving African Americans with hypertension [127]. At this sample size and with similar design assumptions, effect sizes were estimated using the RiSE pilot study for the hypothesized mediator of coping as well as biomarkers [48]. The estimates from the analysis of covariance (Table 4) represent the lower limits for power because the mixed model approach that incorporates all time points may be more powerful in detecting meaningful differences.

**Table 4 table4:** Pilot study estimates and effect sizes.

Outcome evaluated at 6 months	RiSE^a^ group, mean	Control group, mean	|Δ|, mean	Pooled SD	Observed effect size	Mean difference required for 80% power^b^
WCQ^c^: active coping	23.76	24.77	1.01	8.24	0.06	2.45
WCQ: avoidance coping	8.14	14.38	6.24	5.25	0.59	1.56
WCQ: minimize situation	11.21	14.04	2.83	4.36	0.32	1.30
TNF-α^d^	0.95	1.00	0.05	0.36	0.07	0.11
hsCRP^e^	3.83	7.24	3.41	6.30	0.27	1.88

^a^RiSE: Resilience, Stress, and Ethnicity.

^b^Assumes n=125 per group and α=.05; R-squared value of 5 covariates is 0.30.

^c^WCQ: Ways of Coping Questionnaire.

^d^TNF-α: tumor necrosis factor–alpha.

^e^hsCRP: high-sensitivity C-reactive protein.

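### The article names one primary end point (stress at 6 months, powered as the PSS) but its analysis section labels nine outcomes primary, so it disagrees with itself on what makes the trial positive

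*Protocol article*

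**What the plan says.** Two places give a single primary end point. The abstract's Methods paragraph says "The primary end point will be stress at 6 months after the intervention", without naming a scale. The Sample Size section supplies the scale with the words "For the primary end point of the Perceived Stress Scale (PSS". It then bases power on one analysis-of-covariance F test of that score at α=.05, in 250 participants expected to have 6-month data.

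The Statistical Analysis section gives a wider list: "The primary DVs include stress-related symptoms (current perceived stress, depressive symptoms, fatigue, and sleep disturbance) and biomarkers". The biomarkers are then spelled out: "ie, IL-6, TNF-α, IL-1β, IFN-γ, and CRP) to be modeled using GLMM". The count is four constructs plus five biomarkers, nine in all. The model is the same for each: "For each DV, a GLMM will regress the follow-up DV on a group×time interaction, the baseline value of the DV, and covariates". Only a further group is ranked lower: "Exploratory end points include coping (Ways of Coping Questionnaire and Coping with Discrimination Scale), internalizing racism (Appropriated Racial Oppression Scale), and resistance to racism". No secondary tier is named.

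Table 3 lists two instruments for the construct that carries the primary end point: "Current perceived stress: Perceived Stress Scale [104] and Stress Overload Scale [105". It also lists two for depression, the Beck Depression Inventory and "depressive symptoms: Patient Health Questionnaire-9 [106". The Statistical Analysis section promises a detailed statistical analysis plan (SAP) before database lock. That plan is not shown.

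**The concern.** The primary designation decides which result the trial stands or falls on. Someone writing the SAP from the Sample Size section would specify one confirmatory test, PSS at T3. Someone writing it from the Statistical Analysis section would specify nine, each on a group-by-time interaction, with no visit marked as decisive. Both could claim to follow the published protocol, and a later report could do the same.

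This matters most if PSS at 6 months is not significant while another symptom scale or a cytokine is. On one reading the trial is then negative. On the other, a primary outcome has been met. Enrolment had reached 120 of the planned 300 by March 2025, so the point is best settled before outcome results are known.

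**Working it through.** **1. The stated power, as one PSS test.** Inputs from the Sample Size section: 125 per arm, difference 3 points, SD 10, R² = 0.3 for 5 covariates, α = .05.
- Residual SD = 10 × √(1 − 0.3) = 8.37.
- Noncentrality = (125/2) × (3/8.37)² = 8.04.
- Error degrees of freedom = 250 − 2 − 5 = 243.
- Power of the F test on 1 and 243 df = 80.6%.

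The stated figure of more than 80% is reproduced for a single test of PSS at .05. An F test on 1 df is non-directional, so this corresponds to a two-sided .05 test. The planned loss is 50/300 = 16.7%, which takes 250 analysed to 300 enrolled.

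**2. The sections side by side.**

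| Section | Primary outcome | Visit | Test |
|---|---|---|---|
| Abstract, Methods | Stress, scale not named | 6 months | Not tied to one test |
| Sample Size | PSS | 6 months | One F test, α=.05 |
| Statistical Analysis | 4 symptom constructs + 5 biomarkers = 9 | None singled out | Group-by-time model for each |

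The fitted model could yield a T3 contrast. The text does not say that this contrast is the primary test.

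**3. What the wider reading would imply, if any one of the nine counted.** Under independence, 1 − 0.95⁹ = 1 − 0.630 = 37.0%. The outcomes are surely correlated, but the documents give no correlations, so the values below are assumptions. They use equicorrelated normal test statistics, each tested two-sided at .05.

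| Assumed common correlation | Chance of at least one false positive among 9 |
|---|---|
| 0 | 37% |
| 0.3 | 33% |
| 0.5 | 27% |
| 0.8 | 17% |
| PSS at T3 the only confirmatory test | 5% |

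**4. What keeping nine primaries would cost under one simple correction.** Flat Bonferroni gives α = .05/9 = .0056. The same F test for PSS then has 52% power at SD 10. At the SD of 7.2 that the Sample Size section also cites, the residual SD is 7.2 × √0.7 = 6.02 and power is 87%. The cost depends heavily on the SD.

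**The case against.** The best defence is that the nine outcomes are simply those of the article's primary aim. The Conceptual Model section pairs symptoms and biomarkers in that aim and makes coping the subaim, and Table 3 groups the nine under Aim 1. On this reading, PSS remains the one primary end point and the Statistical Analysis section is only loosely worded. That is plausible and may be what was meant. But the text does not say so, and the same section ranks coping and the racism scales as exploratory. A reader will therefore take its labels as a hierarchy.

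Four stronger inferences are tempting, and the documents do not support them.
- **That the trial plans a 37% error rate.** No section says that one significant result among nine makes the trial positive. The only test tied to an alpha for the primary end point is PSS at .05. The article also undertakes to report all preplanned analyses and to label post hoc ones.
- **That the lack of a multiplicity procedure is a fault.** That choice can properly be left to the promised SAP.
- **That there are eleven primary variables.** The analysis section names constructs. Table 3 is a schedule of measures and does not say that both instruments for a construct are modelled as primary.
- **That several primaries are unaffordable at 300 participants.** The 52% figure holds only for flat Bonferroni at the SD of 10 that the article calls conservative. A fixed sequence starting with PSS would leave PSS power unchanged.

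**Conclusion.** The inconsistency stands. It lies in the current text and is not a matter of missing detail: one primary end point in the abstract and Sample Size section, nine in the Statistical Analysis section, and no 6-month contrast designated there. The sample size calculation is correct for a single PSS end point.

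The possible inflation, from 5% to between about 17% and 37%, rests on two assumptions: that any one of the nine at .05 would be claimed as success, and that the outcomes share a common correlation between 0.8 and 0. It shows what the ambiguity leaves open and is not an error rate the trial has adopted. Which outcome is primary should be settled now, because it decides whether any multiplicity adjustment is needed at all.

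**What to change.** In the Statistical Analysis section, name the between-group difference in PSS at T3 as the sole primary outcome, tested at two-sided .05. Relabel the other symptom measures, including the Stress Overload Scale, and the five biomarkers as secondary. Say that the primary test is the T3 contrast from the PSS model. Coping, internalized racism and resistance stay exploratory.

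This brings the section into line with the abstract and the Sample Size section. It changes wording only: 300 enrolled, α=.05 and 80.6% power all stay. The price is that depressive symptoms, fatigue, sleep disturbance and the biomarkers lose primary status. Any multiplicity procedure for them can be set in the SAP. If the sponsor does want several primary outcomes, the protocol should state the success rule and show a sample size that matches it.

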**Exclusion criteria**
History of myocardial infarction or ischemic heart disease and angina pectoris, stent placement, coronary artery bypass, left ventricular hypertrophy, congestive heart failure, or ischemic strokeAny major immune-related disease (eg, rheumatoid arthritis or lupus)Use of immune-altering medications, such as glucocorticoidsPeriodontal disease, bleeding gums, and dental work in the past 72 hCurrent smoker or has smoked in the past 3 moActive cancerActive infectionSubstance abuseCognitive or psychiatric disorder that would affect the ability to participate in program classes (Brief Screen for Cognitive Impairment total score of ≥8)

Participants will be assessed for CMD risk. They will also be assessed for cognitive impairment using the 3-item Brief Screen for Cognitive Impairment [71]: a total score of ≥8, which suggests cognitive impairment, will lead to the exclusion of the participant from the study. All ineligible participants will receive a gift card (US $10) after the screening. Baseline measures will be collected after the screening.

After the baseline interview (T0), eligible participants will be randomized 1:1 to RiSE or HEP, with each wave of enrollment treated as a block. The randomization plan (PROC PLAN) generated in SAS 9.4 (SAS Institute Inc) includes the site as a stratifying variable, and we plan for each site to have at least 6 RiSE and 6 control participants per wave. Patient registration data, group assignment, and self-report survey data will be managed via a single REDCap (Research Electronic Data Capture; Vanderbilt University) server with access for both sites.

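### With a single baseline term for all three follow-up visits, the mixed model as written is not guaranteed to be at least as precise at 6 months as the ANCOVA whose power is called a lower limit

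*Protocol article*

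**What the plan says.** The Abstract places the primary end point at the last visit: "The primary end point will be stress at 6 months after the intervention". The follow-up visits are listed in Statistical Analysis as "T1: midintervention; 4 wk, T2: intervention completion; 8 wk, and T3: 6 mo after intervention completion". The last visit (T3) is therefore about 8 + 26 = 34 weeks from the start of the programme.

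The same section gives the model: "For each DV, a GLMM will regress the follow-up DV on a group×time interaction, the baseline value of the DV, and covariates". Group is the only term said to interact with time. On the remaining structure it says: "Time will be modeled as a fixed effect, and random intercepts and random slopes will be considered". It does not say whether time is categorical, and it does not fix the within-person covariance.

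The Sample Size section rests on an ANCOVA at one visit. It expects 250 of 300 participants to have 6-month data and states that "this sample size has >80% power to detect a 3-point difference in mean PSS scores at follow-up", with SD 10, R-squared 0.30 for five covariates including baseline PSS, and alpha 0.05. It then says that the ANCOVA estimates in Table 4 "represent the lower limits for power because the mixed model approach that incorporates all time points may be more powerful". Table 4 lists three coping scores, TNF-α and hsCRP at 6 months. It has no PSS row.

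**The concern.** An ANCOVA at 6 months estimates its own baseline slope for that visit. The stated mixed model estimates one slope from weeks 4 and 8 and month 6 together. A baseline score may well track a 4-week score more closely than one taken 34 weeks later. If so, the pooled slope is too steep for the visit that carries the primary end point. The excess slope leaves baseline variation in the 6-month contrast that the ANCOVA would have removed.

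Using all visits therefore does not by itself make the mixed model at least as powerful as the ANCOVA. Early visits can add information, and a pooled slope can take some away. At stake is a little precision on the primary contrast, and the accuracy of a sentence that tells the reader the power figures can only be understated.

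**Working it through.** **1. The plan's own figure.** Inputs from Sample Size: difference 3, SD 10, R-squared 0.30, n = 125 per arm, alpha 0.05. The noncentrality is (n/2) × 3² / [10² × (1 − 0.30)] = 62.5 × 9 / 70 = 8.04. With 250 − 2 − 5 = 243 error degrees of freedom, the F test has 80.6% power. The statement of more than 80% reproduces. The last column of Table 4 also reproduces (2.45, 1.56, 1.30, 0.11, 1.88). Those differences are defined at exactly 80% power.

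**2. Cost of a pooled slope.** In SD units, let b be the pooled slope and b3 the slope at 6 months. With categorical time and complete data, the large-sample variance of the 6-month contrast, relative to the ANCOVA, is

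ratio = 1 + (b − b3)² / (1 − R²), with 1 − R² = 0.70.

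With a random intercept only, b is the mean of the three slopes. With unstructured covariance, b is the generalised-least-squares weighted slope. Power follows by dividing the noncentrality of 8.04 by the ratio.

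**3. Assumed correlations.** The article gives none by visit. I assume equal SDs, and correlations between follow-up visits of 0.75 (T1-T2), 0.55 (T1-T3) and 0.60 (T2-T3). I vary the baseline correlations. The value 0.548 is √0.30, which credits the whole R-squared to baseline PSS.

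| Baseline correlation at T1/T2/T3 | b, random intercept / unstructured | Variance ratio | Power |
|---|---|---|---|
| 0.548/0.548/0.548 | 0.548 / 0.548 | 1.000 / 1.000 | 80.6% / 80.6% |
| 0.60/0.575/0.548 | 0.574 / 0.574 | 1.001 / 1.001 | 80.6% / 80.6% |
| 0.70/0.65/0.548 | 0.633 / 0.641 | 1.010 / 1.012 | 80.2% / 80.1% |
| 0.75/0.70/0.548 | 0.666 / 0.685 | 1.020 / 1.027 | 79.8% / 79.6% |
| 0.80/0.75/0.548 | 0.699 / 0.737 | 1.033 / 1.051 | 79.3% / 78.7% |
| 0.80/0.70/0.40 (steep) | 0.633 / 0.742 | 1.078 / 1.168 | 77.6% / 74.3% |

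Example, fifth row, unstructured: (0.737 − 0.548)² / 0.70 = 0.051. At SD 10, power drops below 80% once the ratio passes about 1.016, that is, once b − b3 exceeds √(0.016 × 0.70) ≈ 0.105.

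**4. Missing 6-month data.** The plan expects 300 − 250 = 50 participants without T3. I compared variances with the completers' ANCOVA by simulation (25 per arm missing T3, 1,500 replicates, unstructured covariance). Baseline correlations ranged from nearly flat (0.60/0.575/0.548) to steep (0.70/0.60/0.30).

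| Data from those without T3 | One baseline slope | Visit-specific slopes |
|---|---|---|
| T1 and T2 all present | 0.98 to 1.03 | 0.92 to 0.98 |
| Staggered dropout | 0.99 to 1.06 | 0.97 to 0.99 |
| No follow-up at all | 1.00 to 1.13 | 1.00 |

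These ratios carry Monte Carlo error of roughly 0.02. With complete data and visit-specific slopes, the T3 contrast equals the ANCOVA contrast (ratio 1.000).

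**The case against.** **An article compresses its model.** The model is one sentence, time coding and covariance are open, and a detailed analysis plan is promised before database lock. A baseline-by-time term could be set there. This stands, so the article cannot be said to exclude the term. But it does state the fixed effects and then makes a power comparison about that model, and the comparison has to hold for what is stated.

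**The correlations are assumed.** This stands in full. R-squared 0.30 refers to five covariates jointly. Neither the size nor the net direction of the effect can be settled from the article.

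**SD 10 is called conservative.** This also stands. By the formula in step 1, power is 88.0% at SD 9, 94.2% at SD 8 and 97.5% at SD 7.2. With 5.1% more variance these become 86.4%, 93.1% and 96.9%. A reader might infer that the trial is underpowered for PSS, and the article does not support that. A smaller SD does not, however, make the mixed model at least as precise as the ANCOVA.

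**The lower-limit sentence is about Table 4 and is hedged.** This is correct: there is no PSS row, and the reason offered is only that the mixed model may do better. Extending it to PSS is an inference from the shared design assumptions. The sentence still applies directly to the Table 4 outcomes, which are to be analysed with the same form of model.

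**Bias.** A reader might infer a biased treatment effect. Under 1:1 randomisation the contrast is unbiased whatever the common slope. Over-correction of a chance baseline imbalance is already counted in the variance ratio and is not a separate harm.

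**Conclusion.** The point holds as a modest matter of precision. For the model as written, the ANCOVA is not guaranteed to be a lower limit for power. Under moderate assumed decay with complete data, the 6-month contrast has about 1% to 5% more variance than the ANCOVA, and power at SD 10 is about 80.2% to 78.7% instead of 80.6%. Steeper decay costs more, and equal slopes cost nothing. Where participants without 6-month data have contributed earlier visits, the loss is partly or fully offset, and the common-slope model can even come out slightly ahead.

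The stronger reading, that a common slope always cancels or outweighs what the early visits add, is not supported. The simulated ratios fall on both sides of 1. The result rests on categorical time, equal SDs and the visit correlations stated above. A linear time term would define a different 6-month contrast.

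**What to change.** In the analysis plan, treat time as categorical and specify group, time, group-by-time, baseline, baseline-by-time and covariates. Take the RiSE minus HEP contrast at 6 months from that model, preferably with an unstructured covariance. The 6-month adjustment then matches the ANCOVA used for power. In every scenario run with this term the variance ratio was at or below 1.00, so the lower-limit statement becomes defensible.

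The cost is one model term with 2 degrees of freedom, with no new data and no more participants. If the single baseline term is kept, remove the lower-limit wording, or state that it depends on the baseline association being similar at all three visits.
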